**Table 10. Dose modification principles for aumolertinib in case of treatment-related AEs**

|                                   | Treatment-related AEs                                                                                                                                                 | Dose modification                                                                                                                                                                                                                                                                                                                                                                                                                                                                                                                                                                                    |
|-----------------------------------|-----------------------------------------------------------------------------------------------------------------------------------------------------------------------|------------------------------------------------------------------------------------------------------------------------------------------------------------------------------------------------------------------------------------------------------------------------------------------------------------------------------------------------------------------------------------------------------------------------------------------------------------------------------------------------------------------------------------------------------------------------------------------------------|
| Heart                             | Corrected QT (QTcF) interval > 500 ms observed in at least 2 separate ECG assessments                                                                                 | Interrupt the study treatment for a maximum of 3 weeks*. 
 
If the baseline QTcF interval is > 480 ms and the abnormal value improves to the baseline level within 3 weeks, resume the study treatment at 55 mg;
 
If the baseline QTcF interval is ≤ 480 ms and the abnormal value improves to the baseline level within 3 weeks: 
 
Resume the study treatment at the original dose for the first occurrence;
 
Resume the study treatment at one dose level lower if it reoccurs.
 
 
 
 |
|                                   | QTcF interval prolonged in combination with any of the following: symptoms or signs of torsade de pointes, polymorphic ventricular tachycardia, or serious arrhythmia | Permanently discontinue the study treatment.                                                                                                                                                                                                                                                                                                                                                                                                                                                                                                                                                         |
|                                   | Absolute asymptomatic left ventricular ejection fraction (LVEF) < 50% with a decrease of > 10% relative to baseline                                                   | Interrupt the study treatment for a maximum of 3 weeks*. If the LVEF improves to the baseline level within 3 weeks: 
 
Resume the study treatment at the original dose for the first occurrence;
 
Resume the study treatment at one dose level lower if it reoccurs.
 
                                                                                                                                                                                                                                                                          |
|                                   | Symptomatic congestive cardiac failure                                                                                                                                | Permanently discontinue the study treatment.                                                                                                                                                                                                                                                                                                                                                                                                                                                                                                                                                         |
| Blood creatine phosphokinase (CK) | ULN < CK value ≤ 5 × ULN (Grade ≤ 2)                                                                                                                                  | If no significant muscular symptoms # are observed (Grade ≤ 2), the dose may not be modified.                                                                                                                                                                                                                                                                                                                                                                                                                                                                                             |
|                                   | 5 × ULN < CK value ≤ 10 × ULN (Grade 3), regardless of muscular symptoms #                                                                                 | Interrupt the study treatment for a maximum of 3 weeks*. If the value improves to Grade ≤ 2 (5 × ULN) within 3 weeks: 
 
Resume the study treatment at the original dose for the first occurrence;
 
Resume the study treatment at one dose level lower if it reoccurs.
 
                                                                                                                                                                                                                                                                        |
|                                   | CK value > 10 × ULN (Grade 4), regardless of muscular symptoms #                                                                                           | Interrupt the study treatment for a maximum of 3 weeks*. If the value improves to Grade ≤ 2 (5 × ULN) within 3 weeks: 
 
Resume the study treatment at one dose level lower for the first occurrence;
 
Permanently discontinue the study treatment for the second occurrence.
 
                                                                                                                                                                                                                                                                 |
|                                   | Muscular symptoms # (Grade ≥ 3), with or without CK increased                                                                                              | Interrupt the study treatment for a maximum of 3 weeks*. If the muscular symptoms improve to Grade ≤ 2 within 3 weeks: 
 
Resume the study treatment at the original dose for the first occurrence;
 
Resume the study treatment at one dose level lower if it reoccurs.
 
                                                                                                                                                                                                                                                                       |
| Others                            | Grade ≥ 3 adverse reactions                                                                                                                                           | Interrupt the study treatment for a maximum of 3 weeks*. If the adverse reaction improves to Grade ≤ 2 within 3 weeks: 
 
Resume the study treatment at the original dose for the
 
                                                                                                                                                                                                                                                                                                                                                                     |

|                                                                                                                                                           |  |                                                                                           |
|-----------------------------------------------------------------------------------------------------------------------------------------------------------|--|-------------------------------------------------------------------------------------------|
|                                                                                                                                                           |  | first occurrence;
• Resume the study treatment at one dose level lower if it reoccurs. |
| At any time, if 55 mg is still intolerable (occurrence of Grade $\geq 3$ adverse reactions), permanent discontinuation of study treatment is recommended. |  |                                                                                           |

Note: The severity mentioned above is graded according to the National Cancer Institute - Common Terminology Criteria for Adverse Events Version 5.0 (NCI-CTCAE 5.0). \* If the study treatment is interrupted for more than 3 weeks and the resumption criteria are not met, the study treatment should be permanently discontinued. # Muscular symptoms (including but not limited to): muscle pain, muscle tenderness, muscle twitching, or muscle weakness. When several AEs occur simultaneously, the dose should be modified according to the most severe AE; once the dose is reduced, it cannot be returned to the previous level. Subjects who discontinue treatment should be observed until the resolution of toxicity; dose interruption does not affect scheduled tumor evaluation. The above decisions should be made in agreement between the investigator and the funder.

For certain patients, if the investigator decides to adopt measures such as continuing treatment without interruption, interrupting treatment, modifying the dose, or permanently discontinuing the study treatment, not in accordance with the dose modification provisions of this section, but based on the benefit/risk considerations, agreement should be reached with the funder.

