#### 11.4.2 Dose modifications associated with adverse events

If a subject experiences any toxicity of CTCAE Grade  $\geq 3$  and/or any toxicity (any grade) deemed unacceptable by the investigator, which is judged by the investigator to be treatment-related, the study treatment should be interrupted, and supportive care should be provided as needed in accordance with local practices/guidelines. If the toxicity is relieved or returns to  $\leq$  CTCAE Grade 1–2 within 3 weeks after onset, the IMP at the original dose or dose reduction therapy 1 in Table 7 may be given again. If the original dose is resumed, the subject should be closely monitored for 3 days; if the same toxic effect occurs within 3 days, dose reduction therapy 1 should be considered. Decisions should be made in agreement between the investigator and the sponsor.

If the toxicity does not recover to  $\leq$  CTCAE Grade 1–2 within 3 weeks after onset, dose reduction therapy 2 should be considered. If the toxicity still does not recover to  $\leq$  CTCAE Grade 1–2 within 3 weeks or the same toxic effect

occurs within 3 days, the subject should be withdrawn from the study and should be followed up until the toxicity is recovered.

"Treatment-related" herein refers to definitely related, possibly related, and indeterminable, not including unlikely related and not related. Specific dose modification principles are presented in Table 10.

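### Section 11.4.2 names the sponsor in its text but the funder in the Table 10 notes for agreeing dose decisions, and its set-aside clause does not except three permanent stops

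*Protocol*

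**What the plan says.** Section 11.4.2 of the protocol has a running text followed by Table 10 and its notes.

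- **Text.** After describing interruption and resumption at the original dose or at dose reduction therapy 1 (110 mg, Table 9), it states: "Decisions should be made in agreement between the investigator and the sponsor".
- **Notes to Table 10.** After rules on interruption, reduction and discontinuation, they state: "The above decisions should be made in agreement between the investigator and the funder".
- **Set-aside clause (last note).** It applies to certain patients "if the investigator decides to adopt measures such as continuing treatment without interruption", and also to interrupting, changing the dose or stopping. For measures "not in accordance with the dose modification provisions of this section, but based on the benefit/risk considerations, agreement should be reached with the funder".
- **Permanent stops in the table.** Two Heart rows carry the instruction "Permanently discontinue the study treatment": QTcF prolongation with torsade, polymorphic VT or serious arrhythmia, and symptomatic congestive cardiac failure. The Grade 4 CK row says "Permanently discontinue the study treatment for the second occurrence".
- **Toxicity unresolved at 3 weeks.** The notes say "If the study treatment is interrupted for more than 3 weeks and the resumption criteria are not met, the study treatment should be permanently discontinued". The text of the same section says that dose reduction therapy 2 (55 mg, Table 9) should then be considered.

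The synopsis gives the hospital as sponsor. Sections 8.4 and 11.2 list the sponsor and the funder side by side as two parties to be told.

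**The concern.** Two sentences in one section assign the same kind of decision to different outside parties. The text points the reader to Table 10 for the detailed principles, so a site may well work from the table and its notes. Such a site would resume or reduce the drug with the funder's agreement and miss the sponsor's, which the text requires. A site working from the text alone would miss the funder's.

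The set-aside clause matters more for safety. It follows a table that orders permanent discontinuation for life-threatening cardiac events and for repeated severe CK elevation, yet it is written without exceptions. Read as it stands, it allows dosing to go on in those situations on benefit/risk grounds with the funder's agreement. It does not itself ask for the sponsor's. The trial gives 165 mg, above the 110 mg chosen for the phase II extension (section 4.2.4), so the rules for handling toxicity carry weight.

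The 3-week inconsistency leaves unclear whether a patient whose toxicity has not resolved may go back on drug at all.

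**Working it through.** No sample-size or error-rate figure bears on this point, so the check compares the provisions and counts them.

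**1. Who must agree.** Section 11.4.2 has three agreement sentences:
- text: investigator and sponsor
- Table 10 notes: investigator and funder
- set-aside clause: funder

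That is 1 naming the sponsor and 2 naming the funder (1 + 2 = 3), with 0 naming both. The two words are not interchangeable here, because sections 8.4 and 11.2 name both parties where both are meant.

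**2. What the set-aside clause reaches.** Table 10 has 4 Heart rows, 4 CK or muscular-symptom rows and 1 row for other reactions: 4 + 4 + 1 = 9 event rows. Permanent stops among them:
- ordered at once: 2 rows (QTcF prolongation with torsade, polymorphic VT or serious arrhythmia; symptomatic congestive cardiac failure)
- ordered at the second occurrence: 1 row (CK above 10 × ULN, Grade 4)

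This gives 2 + 1 = 3 stops that nothing else in section 11.4.2 contradicts. The clause covers the dose modification provisions of the section, lists continuing without interruption among the permitted measures, and states no exception. All three stops therefore fall within its wording.

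**3. Whether section 14.2 closes the gap.** Section 14.2 restricts departures from the protocol and asks for consultation with the medical monitor. The set-aside clause is itself part of the protocol, so using it need not count as a deviation. Section 14.2 also does not bring in the sponsor's agreement. It does not clearly close the gap.

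**4. The 3-week rule.** Take a patient with a Grade 3 reaction in the row for other events that is still Grade 3 after 3 weeks. Under the text, 55 mg should be considered. Under Table 10, resumption requires improvement to Grade 2 or lower, and the note orders permanent discontinuation once the interruption exceeds 3 weeks without it. The text opens an option that the note closes.

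**The case against.** The strongest reply is that the first part is only a wording mismatch. A site that obtains both agreements satisfies both sentences, and neither forbids what the other asks. That stands: the sentences are compatible, and the defect is that neither tells the site to obtain both. Likewise, the clause's silence about the sponsor does not show that the sponsor's agreement is waived; the sentence in the text can be read as still applying to decisions to resume or reduce.

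The framing is also softer than the table's imperatives suggest. Section 11.4 is headed as recommended toxicity management, Table 9 as guidelines and Table 10 as principles. The clause is limited to certain patients, requires benefit/risk grounds and a party outside the site, and covers more cautious action as well. Nothing in the protocol says that permanent stops can never be set aside. This tempers the point, but the instructions for the three stops are unqualified, and the table marks a difference elsewhere: for intolerance at 55 mg it says only that "permanent discontinuation of study treatment is recommended".

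Other safeguards exist. Under section 11.1.11, SAEs go to the marketing authorization holder within 24 h, and follow-up SAE information goes to the sponsor and the funder within 24 h. Section 4.3.1 allows an immediate halt, and section 7.8.1 lets the investigator or funder end a patient's treatment. These are routes for notification and stopping; they do not require the sponsor's agreement before dosing continues.

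A reader might infer that the clause overrides four mandatory stops by adding the 3-week rule. The documents do not support that count, because the text of 11.4.2 allows dose reduction therapy 2 to be considered at that point. A reader might also infer that the stops for interstitial lung disease and corneal ulcer can be set aside. Those stand in sections 7.6, 7.8.1, 10.1.13 and 11.4.5, outside the clause if its reference to this section means 11.4.2.

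**Conclusion.** The point holds in three limited parts. First, section 11.4.2 is inconsistent on whose agreement dose decisions need: 1 sentence names the sponsor, 2 name the funder and none names both. Second, the set-aside clause reaches 3 uncontested permanent stops without exception and names only the funder. Third, the text and the Table 10 notes disagree on toxicity unresolved at 3 weeks.

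This rests on reading the clause's scope as the whole of section 11.4.2, and on sponsor and funder being distinct, as the protocol's usage shows. How often the clause would be used cannot be derived from the document. The issue concerns patient safety and consistent conduct; it does not touch the sample size or the primary analysis. The changes are small and worth making.

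**What to change.** - Name the investigator, the sponsor and the funder in all three agreement sentences of 11.4.2. Add that an interruption or stop for safety may be made first and agreed afterwards.
- State that the set-aside clause cannot be used for any less cautious action than Table 10 requires in three cases: QTcF prolongation with torsade, polymorphic VT or serious arrhythmia; symptomatic congestive cardiac failure; and a second Grade 4 CK elevation. More cautious departures stay available.
- Make the 3-week rule the same in text and notes, preferably permanent discontinuation as the notes have it, and then add it to the exclusion.

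The cost is a protocol wording change, an additional contact per decision and slightly less investigator flexibility. Allowing a safety stop to be agreed afterwards keeps the added agreement from delaying protective action.

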#### 11.4.3 Skin reaction

In order to reduce the probability or severity of skin reactions in subjects, it is recommended that subjects be protected against light from the start of study treatment to 3–4 weeks after the last dose.

If a subject experiences any skin reaction, the following formulations may be used based on the investigator's evaluation: steroid cream, topical or systemic anti-inflammatory drugs, topical antihistamines, or retinoid cream. If necessary, symptomatic treatments can be provided.

Skin reactions should be recorded in the AE section of the medical record, and the following information should be included:

- Changing characteristics of the skin reaction.
- CTCAE grade of the skin reaction.
- When necessary, images should be taken to document the skin reactions, and these images should be reviewed by external experts.
- When necessary, skin biopsy may be performed.

#### 11.4.4 Gastrointestinal toxicity

When a subject experiences nausea and/or vomiting, antiemetic therapy can be used for control. In case of a CTCAE Grade  $\geq 3$ , clinically significant, or intolerable diarrhea that the investigator believes is related to the study medication, necessary management or dose modification can be made. This should be recorded in the AE section of the medical record.

#### 11.4.5 Interstitial lung disease

If new or worsening pulmonary symptoms (e.g., dyspnea) are observed or an imaging abnormality suggests the presence of interstitial lung disease, study treatment should be interrupted and the funder should be notified.

All diagnosis results (including HRCT, blood and sputum cultures, and hematology parameters) of the patients will be investigated by the study personnel. The investigator is strongly advised to perform a thorough diagnostic workup on patients to rule out other causes such as lymphangitic carcinomatosis, infection, allergy, edema due to cardiac disease, or pulmonary hemorrhage.

The diagnosis of interstitial lung disease should be considered if confirmed by HRCT scans and other causes of respiratory symptoms have been ruled out, and study treatment should be permanently discontinued. In the absence of a diagnosis of interstitial lung disease, treatment may be resumed after comprehensive safety assessment by the investigator.

A subject who is determined to have developed interstitial lung disease should permanently discontinue the study treatment.

## 12.0 ENDPOINT EVALUATION AND STATISTICAL ANALYSIS

### 12.1 Anti-Tumor Activity Evaluation

#### 12.1.1 Investigator assessment as per RECIST 1.1

At each visit, the investigator will assess the patient's tumor response to treatment as CR, PR, SD, or PD as per RECIST 1.1 by comparing with baseline and previous assessments, depending on patient's status. The progression of TLs will be calculated by comparing with tumor burden at its nadir (i.e., the smallest sum of previously recorded diameters). In the absence of progression, tumor response (CR and PR) and stable disease (SD) will be calculated by

comparing with baseline tumor measurements obtained prior to the start of the treatment. For patients with indeterminable tumor status, if there is evidence of progression, they will be considered to have PD; if there is no evidence of progression, they will be considered inevaluable (NE). The endpoints of this study will be analyzed based on the tumor response assessment by the investigator per RECIST 1.1, and the investigator will also manage subjects only based on the assessment results.

The investigator will evaluate patient's response to treatment using RECIST 1.1 (see Appendix D) by determining the objective response rate (ORR), disease control rate (DCR), duration of response (DOR), and progression-free survival (PFS). In addition to the overall tumor imaging evaluation performed by the investigator as per RECIST 1.1, for systemic and/or intracranial lesions (no more than 5 target lesions in the whole body) selected for overall evaluation, the respective intracranial and systemic response evaluation (intracranial: iPFS, iORR, iDCR, and iDoR; systemic: PFS, ORR, DCR, and DoR) will be performed according to the response evaluation criteria in RECIST 1.1, and the investigator does not need to select additional lesions.

